## Abstract

**Background:**

Multi-professional cooperation between healthcare providers is a key quality criterion of hospice and palliative care. While hospice and palliative care networks can support cooperation on a local level, opportunities for wider cooperation through the establishment and development of regional hospice and palliative care networks in Germany have not yet been explored systematically.

**Aims:**

The HOPAN study aims at: (1) identifying regional hospice and palliative care networks in Germany, (2) analysing these networks using an adapted quality assessment tool, and (3) proposing setting-sensitive recommendations for network development and exploring the benefits of these recommendations.

**Methods:**

HOPAN is a prospective, observational, mixed-methods study comprising three work packages (WPs). In WP1, the stock of regional hospice and palliative care networks in Germany will be identified via database, literature, and internet research. In WP2a, focus groups will be conducted to adapt an existing maturity model for healthcare networks to regional hospice and palliative care networks. In WP2b, a questionnaire will be sent to each identified regional hospice and palliative care network to gain insight into their structure and status of development. In WP2c, group discussions will be conducted to develop setting-sensitive recommendations for these networks. Finally, in WP3, these recommendations will be sent to all participating hospice and palliative care networks, and the benefits of the recommendations will be evaluated via a questionnaire.

**Discussion:**

Empirically developed setting-sensitive recommendations should enable the systematic establishment and management of regional hospice and palliative care networks in Germany, considering the specific needs and potential of each network. The study findings are expected to improve the overall development of hospice and palliative care services.

**Trial registration:**

The study was prospectively registered in the German Clinical Trials Register (Deutsches Register Klinischer Studien) (Registration N° DRKS00030629; date of registration: 02 November 2022). The study is searchable under the International Clinical Trials Registry Platform Search Portal of the World Health Organization, under the German Clinical Trials Register number.

## Introduction

Until recently, some federal states in Germany promoted hospice and palliative care networks on a voluntary basis; however, most networks were financed by the donations and fees of network members [1–5]. To improve on this situation, in 2021, the German legislature passed a new law (Gesetz zur Weiterentwicklung der Gesundheitsversorgung/GVWG) providing for the promotion of regional hospice and palliative networks [6]. The aim of this legislation is to improve multi-professional and cross-sectoral cooperation in hospice and palliative care at a regional level, via network coordinators, funded by statutory health insurance [7]. Specifically, coordinators are tasked to: (a) support cooperation and coordination between network members, (b) support joint public relations, (c) initiate and organise further and advanced training programmes, (d) organise regular network meetings, and (e) cooperate with other regional counselling services [8]. The networks should include all providers of general and specialised palliative care in the inpatient and outpatient setting. In Germany, the focus of hospice care is on psychosocial and bereavement support. Hospice care takes place in inpatient hospices, hospice day clinics and outpatient hospice services, which should be integrated into the networks [9].

A comprehensive overview of regional hospice and palliative care networks in Germany is lacking. To date, only two smaller surveys at the level of individual federal states have been conducted [3, 5]. One study published regional recommendations for the implementation and coordination of hospice and palliative care networks [10], showing that the investigated networks differed considerably regarding their stages of development, organisational structures, fields of activity and working methods [4].

In hospice and palliative care, healthcare providers and volunteers must collaborate to improve the quality of life of patients and their families [11]. Cooperation between providers in care networks enables a seamless interplay of all healthcare professionals and volunteers, thereby improving the continuity of patient care [12, 13].

On a regional level, collaboration between healthcare providers in hospice and palliative care seems to positively impact individual casework [14]. According to the literature, regional networks may increase the number of personal meetings between healthcare providers and increase members’ willingness to cooperate [15]. Hence, regional networks may improve inter-professional communication among healthcare providers, evoke confidence in action, reduce stress among employees, ensure the early integration of psychosocial and spiritual support, and reduce the number of hospital admissions [16]. They may also promote joint initiatives for the further development of local hospice and palliative care services and improve the organisation of patient-centred care [14, 15].

Until recently, the establishment and development of regional hospice and palliative care networks in Germany was largely unsystematic. These networks were not integrated into the German healthcare system and structural standards and quality indices for network collaboration and coordination were lacking.

## Materials and methods

### Study aim

The project “HOPAN–Status exploration and analysis of regional hospice and palliative care networks using an adapted quality assessment tool” has the following three objectives:

to identify regional hospice and palliative care networks in Germany,to analyse these networks using an adapted quality assessment tool, andto propose setting-sensitive recommendations for further network development and to explore the benefits of these recommendations.

### Design

HOPAN is a prospective, observational, mixed-methods study organised into three working packages (WPs). The study protocol adheres to STROBE guidelines [17]. WP1 will involve the identification of regional hospice and palliative care networks in Germany via database, literature and internet research. The findings will provide an overview of the number and regional distribution of hospice and palliative networks in Germany.

In WP2a, an existing maturity model for healthcare networks, developed within the INDiGeR research project, will be adapted to accommodate the structures and contents of the identified regional hospice and palliative care networks [18]. The INDiGeR research aimed at identifying the most relevant dimensions of successful network management and developing general recommendations for the implementation and improvement of healthcare and service networks. The project identified four key dimensions of network management: (a) infrastructure, (b) governance, (c) promotion, and (d) moderation (see Fig 1).

**Fig 1 pone.0286583.g001:**
[figure not shown]
Key dimensions of network management from the INDiGeR project [18] (authors’ own translation into English).

The maturity model focuses on the common provision of services from a single network perspective. This methodological tool will be adapted for application to hospice and palliative networks.

In WP2a, a group of experts will be formed on the basis of the survey results (WP1) with the leaders (e.g. coordinators, moderators) of hospice and palliative care networks in Germany and other network experts. Expert group workshops will examine the extent to which the maturity model should be supplemented and modified to accommodate hospice and palliative care networks, and how the four relevant network dimensions (i.e. infrastructure, moderation, governance, promotion) should be specified and operationalised. This specified and adapted maturity model will form the basis for the model-based network analysis in WP2b.

In WP2b, the adopted maturity model for regional hospice and palliative care networks will be operationalised into questionnaire items. Subsequently, an online survey will be administered to all of the identified networks. The survey is expected to comprise three sections:

A general section on the networks’ basic and structural data (e.g. year of founding, number of partners, participating care actors, number of meetings per year).A specific section on the model-based network evaluation, focussing on network dimensions and the degrees identified in WP2a (e.g. for network moderation: role understanding and responsibility, intensity of cooperation, communication, services offered to network members, network culture). Specific items will be associated with each sub-dimension, graded in four levels (e.g. initial, structured, established, optimised). Based on the results, a developmental status will be assigned to each dimension.A retrospective section on good practice and experiences of network development. Each dimension or sub-dimension will be specifically queried, to generate practical examples for the development of recommendations in WP2c.

In WP2c, four expert workshops with the abovementioned network leaders and coordinators (*n* = 10) will be conducted to develop setting-sensitive recommendations for regional hospice and palliative care networks, on the basis of the results from WP2b.

In WP3, the recommendations arising out of WP2c will be disseminated to individual networks and usability will be evaluated. Each network surveyed in WP2b will receive setting-sensitive, individual recommendations, according to the network’s maturity level. Additionally, each network will receive a link to a quantitative, standardised, online questionnaire to evaluate the utility of the recommendations. This questionnaire will be developed a priori by the research team and will contain questions on the usefulness of the recommendations in their respective dimensions, as well as the actual and planned implementation of the recommendations. The link to the online questionnaire will be sent to the networks using the survey software SoSciSurvey (SoSci Survey GmbH, 2006–2022). The primary aim will be to explore the relevance and feasibility of the setting-sensitive recommendations. Finally, the maturity model and its level-specific recommendations will be adapted in accordance with the survey results and prepared for regional hospice and palliative care networks, so it can be used by: (a) further regional hospices and networks for the purpose of self-assessment and (b) health insurance providers for the purposes of quality assessment and reporting.

### Study population and data collection

In WP1, all regional hospice and palliative care networks in Germany will be identified as completely as possible. The total stock of such networks in Germany is currently unknown. Hence, the size of this population can only be estimated. Based on the identified hospice and palliative care networks in Lower Saxony [19] and Bavaria [20], a total of 150 networks in Germany is estimated. Data will be collected via internet and literature research, supplemented by a search of national databases, such as the publicly accessible palliative care portal [21], the “Wegweiser Hospiz- und Palliativversorgung Deutschland” [22], and partly available lists of health ministries and state coordination offices. Network names, contact details, regions, and other relevant and available information (e.g. year of founding, legal formation, sponsorship) will be recorded.

The group of experts, which will be set up in WP2a, will include leaders (*n* = 10; e.g. coordinators, moderators) of hospice and palliative care networks in Germany and other network experts from hospice and palliative care facilities in Germany. Participating network leaders (*n* = 7–8) will be selected from the group of networks identified in WP1. The selection will follow the maximum variation sampling strategy, based on criteria that have not yet been defined (e.g. size, duration of existence, degree of professionalisation). Moreover, a small number of experts (*n* = 2–3) will be recruited from the group of network members, based on the suggestions of cooperating German professional hospice and palliative care associations. If experts decline to participate in the study, the expert group will be supplemented on the basis of the same sampling criteria.

A total of *n* = 5 expert workshops are planned, each involving *n* = 10 of the abovementioned leaders and coordinators. Four of these meetings will be conducted as online video conferences. The first workshop will explore the extent to which the structure of the INDiGeR maturity model should be augmented and modified to accommodate hospice and palliative care networks. Members of the research team will send literature on the maturity model to participants prior to the workshop, and then present the model to participants at the workshop. The subsequent three workshops will aim at concretising and operationalising the assumed relevant network dimensions (i.e. infrastructure, moderation, governance, promotion) for regional hospice and palliative care networks. The documented results of the workshops will be compiled, reflected upon, discussed, and integrated by the research team and further developed into a maturity model for regional hospice and palliative care networks. The developed model will then be presented to the experts for their feedback in a further online workshop. In the expert workshops, established methods for moderating group discussions (e.g. card queries, World Cafe) will be used. Each workshop will be 3 hours in duration, and will be audio recorded and transcribed verbatim.

In WP2b, the respective leaders/coordinators of an estimated *n* = 150 hospice and palliative care networks will be sent an online survey. A response rate of 70% is expected, and thus *n* = 105 valid data sets to include in the analysis. Notwithstanding this calculated response rate, the aim will be to include as many as possible of the networks identified in WP1, in order to increase statistical power, especially for the more detailed network analysis.

In WP2c, expert workshops (*n* = 4) with the abovementioned network leaders/coordinators (*n* = 10) will be conducted to develop setting-sensitive recommendations for regional hospice and palliative care networks. For this purpose, the results of the network analysis for the individual dimensions of the maturity model (including the level-specific locations of the networks) will be presented as impulse speech. In group discussions, participants will develop specific recommendations for the further development of networks for each development level and sub-dimension. Each workshop will be 3 hours in duration, and will be audio recorded and transcribed verbatim. An overlap of participants in WP2a and WP2c will promote participants’ long-term commitment to and identification with the project.

In WP3, all networks that participated in WP2b will be administered a quantitative online survey. A total of *n* = 105 participating networks in WP2b and a response rate of 70% are assumed. Hence, 74 valid data sets are expected for inclusion in the analysis. Respondents will indicate on a 4-point verbal rating scale the extent to which they deem the individual recommendations relevant and feasible for their own network. They will also be afforded the opportunity to make suggestions for improvement, via free text comments.

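### Leaders who help write the recommendations are counted undistinguished among the networks that rate them in WP3, which can bias the only evaluation, plausibly upward

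*Protocol article*

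**What the plan says.** All of the following is in the protocol article; unless another section is named, it is under Study population and data collection.

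- **Who is in the expert group.** Ten experts, most of them network leaders: "Participating network leaders (*n* = 7–8) will be selected from the group of networks identified in WP1". The other 2–3 are recruited from network members.
- **What the group does.** It works on the maturity model in five WP2a workshops. In four WP2c workshops the same leaders and coordinators, again ten, develop recommendations for each level and sub-dimension. Under Data analysis, the research team's part in the recommendations is a coherence review and changes of wording.
- **The overlap is intended.** "An overlap of participants in WP2a and WP2c will promote" lasting attachment of these people to the project, according to the article.
- **Who is surveyed.** WP2b goes to the leaders or coordinators of all identified networks. The evaluation follows from that: "In WP3, all networks that participated in WP2b will be administered a quantitative online survey". Respondents rate on a 4-point scale how relevant and how feasible the recommendations are for their own network. "Hence, 74 valid data sets are expected for inclusion in the analysis".
- **What is not distinguished.** The exclusions under Inclusion and exclusion criteria (language, consent) concern the experts in WP2a and WP2c, not WP3 respondents. Data analysis describes WP3 as descriptive, with no separate reporting of expert-group networks. Limitations of the study design notes that only coordinators' and leaders' views are captured, but not that some of them are also authors.

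**The concern.** WP3 is the only planned evaluation of the recommendations, and its primary aim (Design) is to explore their relevance and feasibility. Its results are used to adapt the model and the recommendations, which are then intended for self-assessment by networks and for quality assessment and reporting by health insurers. A favourable rating from someone who helped write a recommendation is not independent evidence that it is useful elsewhere.

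The article does not simply leave the matter open. It fixes the WP3 population as every network from WP2b and counts the resulting 74 data sets as the analysis set. As planned, the tables would not let a reader separate the authors' ratings from everyone else's.

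The pooled effect is limited, but it is systematic and does not shrink as more networks respond in the same proportions. It would weigh most where few networks rate a given recommendation. That can happen because each network receives recommendations according to its maturity level.

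**Working it through.** **Inputs from the protocol article**

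- Networks: "a total of 150 networks in Germany is estimated".
- WP2b: "A response rate of 70% is expected, and thus *n* = 105 valid data sets to include in the analysis".
- WP3: "A total of *n* = 105 participating networks in WP2b and a response rate of 70% are assumed".
- Expert-group leaders from surveyed networks: k = 7 to 8.
- Four development levels, given as an example under Design.

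**Assumptions (not in the documents)**

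- The same leader answers for the network in WP3.
- All expert-group leaders rate favourably, which is the extreme case.
- The favourable share among the other networks is p = 50% or 70%. The article defines no such summary; it is used here to express size.

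**Step 1. The plan's own figures.** 150 × 0.70 = 105. 105 × 0.70 = 73.5, stated as 74. Both reproduce.

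**Step 2. Share of expert-group networks in WP3**

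- At 70% response in each wave, k × 0.70 × 0.70 = 3.43 to 3.92 networks remain. Divided by 74, this is 4.6% to 5.3%.
- If all respond in both waves: 7/74 = 9.5%, 8/74 = 10.8%.

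**Step 3. Shift in the favourable share.** Shift = share × (1 − p).

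| p among the others | 70% response per wave | All respond (upper bound) |
|---|---|---|
| 50% | 2.3 to 2.6 points | 4.7 to 5.4 points |
| 70% | 1.4 to 1.6 points | 2.8 to 3.2 points |

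On the rating scale itself, the mean moves by share × gap. If these leaders rate one point higher than the others (assumed), that is about 0.05 at 70% response per wave and about 0.10 if all respond.

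**Step 4. A single maturity level.** An even split over four levels (assumed) gives 74/4 = 18.5 raters. With 2 authors among 18 to 19 raters and p = 50%, the shift is 2/19 × 0.5 = 5.3 to 2/18 × 0.5 = 5.6 points.

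**Step 5. Precision with and without these networks.** Half-width of the 95% interval = 1.96 × √(p(1 − p)/n), at p = 70%.

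- n = 74: 1.96 × √(0.21/74) = 10.4 points.
- n = 66 (8 removed): 1.96 × √(0.21/66) = 11.1 points.
- At 70% response per wave, 74 − 3.9 = 70.1 networks remain, and the half-width is 1.96 × √(0.21/70) = 10.7 points.

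These figures count the leaders' networks only, because the surveys go to leaders and coordinators. If the networks of the other 2–3 experts were also surveyed and all responded, the ceiling would be 10/74 = 13.5%.

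**The case against.** The strongest reply is that WP3 is formative. It explores, has no hypothesis, comparator or success threshold, and collects suggestions for improvement. No decision in the article turns on a shift of a few points. Even the upper-bound shift is smaller than the sampling half-width of about 10 to 11 points at 50–70%. Leaders who sat in the workshops also belong to the target population, and each judges only the recommendations sent to their own network, so whether those are feasible locally is legitimate information. Sending the survey to every network is not wrong, and a descriptive analysis does not rule out split reporting.

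Most of this stands, and it limits the size of the problem. It does not remove the overlap: the article counts every data set for inclusion and does not name the overlap as a limitation.

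A reader might infer more than the documents support, in three ways.

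- **That the evaluation is shown to be biased upward.** The only textual support is the stated wish to attach participants to the project. That sentence concerns WP2a and WP2c, and says nothing of WP3 response or ratings. The direction is an inference.
- **That the distortion within a level is dramatic.** One can construct a level with 7 raters, 2 of them authors, in which 50% becomes (0.5 × 5 + 2)/7 = 64%. The article gives no distribution of networks over levels, so this has no source.
- **That expert-group networks must be left out of the main analysis.** They are eligible networks chosen for maximum variation, and whether the main table should omit them is debatable. Showing both results answers the concern.

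**Conclusion.** The point holds as a limited but avoidable weakness. Leaders of 7–8 surveyed networks help write what WP3 evaluates, and their ratings are pooled with the rest, undistinguished and without mention. This can bias the relevance and feasibility results, plausibly upward.

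At the protocol's own response rates the pooled shift is about 1.4 to 2.6 points for favourable shares of 70% and 50% among the other networks. The ceiling is 2.8 to 5.4 points if every expert-group leader responds in both waves. Both ranges assume uniformly favourable ratings from these leaders, so smaller shifts are possible. For a recommendation rated at one level only, about 5 points is reachable under an assumed even split over four levels.

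A clearly favourable or unfavourable overall result would not be overturned. What is weakened is any claim that the recommendations were endorsed by networks that had no part in writing them.

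**What to change.** - Set an indicator, at the latest when WP3 invitations go out, for every network with a member in the WP2a or WP2c expert group.
- Report the WP3 relevance and feasibility tables with and without these networks, overall and by maturity level.
- Base any statement of independent endorsement on the networks without an expert-group member.
- Name the overlap under Limitations of the study design.
- Keep these networks in WP1 and WP2b, and still send them their recommendations and the WP3 questionnaire.

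The cost is one variable and a second set of tables. Counting the leaders' networks only, the independent subset would hold about 66 to 70 data sets instead of 74, with a 95% half-width at 70% of at most about 11.1 points. By-level tables without the flagged networks will be thinner, so counts should be shown beside percentages.
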